### Sample size calculation

There will be 20 participants in the healthy volunteer cohort. To detect a minimum of 50% variance (R^2^) explained by eight MRI variables, at a 0.05 level of significance and minimum power of 0.80, a sample of 24 subjects is required. Therefore, there will be 24 participants in each of the CKD participant derivation and validation cohorts.

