### Outcomes

The primary outcome will be the association between a multiparametric MRI marker and TIF quantified on kidney biopsy with a minimum variance of 50% (R^2^=0.5). The model for the primary outcome will include the following MRI variables: total kidney volume, cortical T1 value, cortical T2 value, cortical T2* value, cortical ADC value, renal artery blood flow, renal perfusion and cortical contrast distribution measures.

The secondary outcomes will include the association between (1) individual MRI variables and TIF, (2) combinations of MRI variables and TIF, based on significant correlations identified in (1), (3) the multiparametric MRI marker for the primary outcome and eGFR and (4) the multiparametric MRI marker for the primary outcome and albuminuria. Exploratory outcomes will include the association between (1) the multiparametric MRI marker for the primary outcome and TIF as a categorical variable and (2) individual MRI variables and TIF as a categorical variable.

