### Data analysis plan

All statistical analyses will be performed using R Statistical Software (V.4.1.3; R Core Team 2022). Continuous variables will be expressed as mean and SD and compared using t-tests for normally distributed data. Skewed data will be expressed as median and IQR and compared using Mann-Whitney U tests. Data normality will be assessed visually using histograms. Categorical data will be compared using χ^2^ tests. The healthy control group will determine normal MRI reference ranges for baseline comparison. All variables (MRI, TIF, eGFR and albuminuria) will be measured and reported as continuous variables for the primary and secondary outcomes. TIF will be reported as a four-level categorical variable for the exploratory outcomes.

For the primary outcome, a multivariable linear regression model including all MRI variables will be fitted to examine the association between the multiparametric MRI marker and TIF. The model will be tested and developed in the CKD participant derivation cohort. Model performance will be assessed using a prespecified minimum variance (R^2^) threshold of 0.50 and p<0.05. Patterns of missing data will be inspected and reported. Where appropriate, multiple imputation will be used to account for missing data under the missing at random assumption, and sensitivity analyses based on complete cases will be performed. A second independent CKD participant validation cohort will be used to evaluate the accuracy and sensitivity of the model using adjusted R^2^. The multivariable linear regression model will be derived using elastic net regularisation and nested resampling cross-validation in order to minimise overfitting. The agreement performance of the model will be reported using adjusted R^2^ with 95% CIs. Similar univariable and multivariable linear regression models will be fitted to examine the association between the MRI variables and TIF, eGFR and albuminuria for the secondary outcomes. All statistical tests will be two-sided and performed at a 0.05 level of significance.

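### The stated minimum power of 0.80 at n=24 assumes fixed predictors; with observed MRI values it is about 0.75, and the calculation does not carry over to the validation cohort

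*Protocol article*

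**What the plan says.** The Sample size calculation section of the protocol article sets the target: "To detect a minimum of 50% variance (R^2^) explained by eight MRI variables, at a 0.05 level of significance and minimum power of 0.80". It concludes that "a sample of 24 subjects is required. Therefore, there will be 24 participants in each of the CKD participant derivation and validation cohorts". It names neither the test nor the null hypothesis.

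The Outcomes section lists the predictors of the primary model: "total kidney volume, cortical T1 value, cortical T2 value, cortical T2* value, cortical ADC value, renal artery blood flow, renal perfusion and cortical contrast distribution". The last item is worded in the plural, so the list comes to eight only if the contrast measures count as one variable.

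The Data analysis plan sets the criterion for the derivation model: "Model performance will be assessed using a prespecified minimum variance (R^2^) threshold of 0.50 and p<0.05". The same section derives the model by elastic net with nested cross-validation, and evaluates it in the second CKD cohort by adjusted R². It describes no hypothesis test for that cohort.

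**The concern.** Three features of the sample size statement need checking.

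- **The power model.** If 24 comes from a test that treats the MRI values as fixed by design, the stated minimum of 0.80 does not describe a study in which those values are sampled along with the patients.
- **The null hypothesis.** The wording about detecting a minimum of 50% variance can be read as power to establish that R² is at least 0.50. A standard calculation gives only the power to reject R²=0 when the true R² is 0.50. Since 0.50 is also the success threshold, the two are easily confused.
- **The validation cohort.** The second 24 is presented as following from the first calculation, although that cohort has a different task: to assess a model already derived.

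At stake is whether readers can take 0.80 at face value, and whether the validation cohort has any stated basis for its size.

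**Working it through.** **Inputs.** From the Sample size calculation: R²=0.50, p=8 predictors, alpha 0.05, n=24. The effect size is f² = 0.50/(1−0.50) = 1.0. The Data analysis plan makes tests two-sided, but the overall F test uses only its upper tail, so this changes nothing.

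**1. Reproducing the plan's figure (fixed predictors).** The overall F test of R²=0 has p and n−p−1 degrees of freedom and noncentrality λ = f²·n. At n=24 the degrees of freedom are 8 and 15, λ = 24 and the critical F is 2.641.

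- n=23: power 0.766
- n=24: power 0.801

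So 24 is the smallest n reaching 0.80, and the plan's number reproduces exactly.

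**2. Random predictors.** If the predictors are sampled with the patients and are multivariate normal, λ is itself random: λ = f²·χ² with n−1 degrees of freedom. Averaging the noncentral F power over that distribution gives:

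| n | fixed | random |
|---|---|---|
| 24 | 0.801 | 0.749 |
| 25 | 0.831 | 0.780 |
| 26 | 0.858 | 0.808 |

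A direct simulation of 100,000 studies at n=24 gave 0.750. The level 0.80 is first reached at n=26.

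**3. A ninth predictor.** If the contrast measures enter as two variables, then at n=24 power is 0.750 with fixed and 0.701 with random predictors.

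**4. The 0.50 criterion in derivation.** The sample R² needed for p<0.05 is pF/(pF + n−p−1) = (8×2.641)/(8×2.641 + 15) = 21.13/36.13 = 0.585. Every significant result therefore already has a sample R² above 0.50. The chance of meeting both conditions equals the power of the F test: 0.801 fixed, 0.749 random.

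If 0.50 is meant as adjusted R², the sample R² must reach 1 − 0.50×15/23 = 0.674. At a population R² of 0.50 with random predictors, the chance of that is 0.495.

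**5. What 24 gives in validation.** The plan states no target for this cohort, so these figures illustrate what a separate justification could use.

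- *One-degree-of-freedom test of the frozen score.* A least-squares model is derived in 24 patients, its score is fixed, and the correlation of score with fibrosis is tested in 24 new patients. With population R² 0.50 and eight independent, equally weighted normal predictors (assumptions), simulated power is about 0.84.
- *Precision.* For an observed squared correlation of 0.50, r = 0.707 and Fisher z = 0.881. The half-width is 1.96/√21 = 0.428. Back-transforming gives r from 0.425 to 0.864; squared, this is about 0.18 to 0.75.

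**The case against.** The strongest reply is that nothing has been miscalculated. The fixed-predictor F test is a common convention, 24 is its correct answer, and the test has the same type I error either way. The random-predictor figure rests on multivariate normality, which the protocol does not assume, and the gap is five points, or two patients. All of that stands. It does not restore 0.80 as a minimum: the fixed-predictor power is conditional on one set of MRI values, and this study does not choose those values.

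A reader might go further and infer that the chance of meeting the 50% target is far below 0.80 because the null is R²=0. The documents do not support that for the derivation criterion as written, since significance at n=24 already requires a sample R² of at least 0.585. It applies only if 0.50 means adjusted, out-of-sample or population R², which the protocol leaves open.

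A reader might also infer that the model is very likely to fail in validation. The Data analysis plan sets no clear 0.50 pass mark for that cohort. The chance of reaching such a mark depends heavily on whether least squares or a penalised fit is used and on how the predictors correlate. The documents fix no single figure.

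Finally, the protocol acknowledges its limited sample size, and 24 can be defended for validation on the frozen-score test. Both are true, but a general acknowledgement does not correct a specific stated power, and the defence available for validation is not the one the protocol gives.

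**Conclusion.** The point holds in a limited form. The stated minimum power of 0.80 is correct only for fixed predictors in an unpenalised model. For observed, multivariate-normal MRI values, power to reject R²=0 at a population R² of 0.50 is about 0.75, five points lower, or about 0.70 with nine predictors. None of these figures describes the elastic net model that the plan will derive.

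The validation cohort is the weaker part of the statement: its size is inferred from a test that is not described for it, so the 0.80 gives it no support. That is a gap in the justification, not proof that 24 is too few.

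Testing R²=0 costs no further power under the literal criterion of sample R² at least 0.50 with p<0.05. If the threshold is meant as adjusted R², the chance of success at a population R² of 0.50 is only about 0.50, so the protocol should say which R² it means.

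**What to change.** Amend the Sample size calculation and leave n unchanged.

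- Name the test and the null. State that 24 participants give about 0.75 power, with random predictors, to reject R²=0 when the population R² is 0.50, for eight predictors in an unpenalised linear model. Let this replace the wording about detecting a minimum of 50% variance.
- Say that this power does not describe the elastic net model, and that it assumes the contrast measures enter as one variable.
- State whether the 0.50 threshold refers to sample or adjusted R².
- Give the validation cohort its own justification: the one-degree-of-freedom test of the frozen score (power about 0.84 under least squares with eight equally weighted predictors, stated as an assumption), and the precision at n=24 (95% CI about 0.18 to 0.75 for an observed squared correlation of 0.50, labelled as squared correlation and not as predictive R²).

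This needs no extra patients and no change of procedure. The price is a stated power about five points less favourable. Recruitment is expected to run to December 2028, so the text can be amended before analysis.

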### Data analysis plan

All statistical analyses will be performed using R Statistical Software (V.4.1.3; R Core Team 2022). Continuous variables will be expressed as mean and SD and compared using t-tests for normally distributed data. Skewed data will be expressed as median and IQR and compared using Mann-Whitney U tests. Data normality will be assessed visually using histograms. Categorical data will be compared using χ^2^ tests. The healthy control group will determine normal MRI reference ranges for baseline comparison. All variables (MRI, TIF, eGFR and albuminuria) will be measured and reported as continuous variables for the primary and secondary outcomes. TIF will be reported as a four-level categorical variable for the exploratory outcomes.

For the primary outcome, a multivariable linear regression model including all MRI variables will be fitted to examine the association between the multiparametric MRI marker and TIF. The model will be tested and developed in the CKD participant derivation cohort. Model performance will be assessed using a prespecified minimum variance (R^2^) threshold of 0.50 and p<0.05. Patterns of missing data will be inspected and reported. Where appropriate, multiple imputation will be used to account for missing data under the missing at random assumption, and sensitivity analyses based on complete cases will be performed. A second independent CKD participant validation cohort will be used to evaluate the accuracy and sensitivity of the model using adjusted R^2^. The multivariable linear regression model will be derived using elastic net regularisation and nested resampling cross-validation in order to minimise overfitting. The agreement performance of the model will be reported using adjusted R^2^ with 95% CIs. Similar univariable and multivariable linear regression models will be fitted to examine the association between the MRI variables and TIF, eGFR and albuminuria for the secondary outcomes. All statistical tests will be two-sided and performed at a 0.05 level of significance.

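### The only success rule (R² of at least 0.50 with p<0.05) reads as applying to the cohort that builds the model, so passing it would not show that the MRI marker explains 50% of fibrosis

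*Protocol article*

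**What the plan says.** The Outcomes section defines the primary outcome as the association between a multiparametric MRI marker and "TIF quantified on kidney biopsy with a minimum variance of 50% (R^2^=0.5"). It names no cohort for that target.

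The Data analysis plan says that "a multivariable linear regression model including all MRI variables will be fitted to examine the association" between the marker and tubulointerstitial fibrosis (TIF). It continues: "The model will be tested and developed in the CKD participant derivation cohort". The next sentence is the rule: "Model performance will be assessed using a prespecified minimum variance (R^2^) threshold of 0.50 and p<0.05". After a passage on missing data it turns to validation: "A second independent CKD participant validation cohort will be used to evaluate the accuracy and sensitivity of the model using adjusted R^2"). No threshold accompanies this. The same paragraph then says that the model is derived with elastic net and nested cross-validation to limit overfitting, and that adjusted R² will be reported with 95% CIs.

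The Sample size calculation gives its aim and inputs as: "To detect a minimum of 50% variance (R^2^) explained by eight MRI variables, at a 0.05 level of significance and minimum power of 0.80". From these it concludes that "a sample of 24 subjects is required". The same number is used twice: "there will be 24 participants in each of the CKD participant derivation and validation cohorts".

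**The concern.** An R² computed in the patients who supplied the coefficients overstates what the model explains in anyone else. With 24 patients and eight predictors the overstatement is large. The study's claim is a quantitative one, that the marker accounts for at least half of the variation in fibrosis. If the rule is read off the derivation fit, it can be met when the true figure is well below one half. The validation cohort, which could correct this, has no stated criterion against which to judge it.

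**Working it through.** **Inputs.** Eight predictors, target R² 0.50, alpha 0.05, power 0.80 and N=24 per cohort (Sample size calculation). The rule is R² ≥ 0.50 and p<0.05 (Data analysis plan). Assumption: the contrast distribution measures enter as one term, giving eight in all.

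**1. Reproducing the plan's figure.** Take the overall F test of R²=0 with fixed predictors, f² = 0.50/(1−0.50) = 1, noncentrality f²·N, and df 8 and N−9. Power is 0.766 at N=23 and 0.801 at N=24. The stated 24 is therefore reproduced exactly, as the power to reject R²=0 in the fitted cohort. With random normal predictors, power at N=24 is 0.749.

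**2. What p<0.05 already demands (unpenalised fit).**
- F(0.95; 8, 15) = 2.641.
- Critical R² = 8F/(8F+15) = 21.13/36.13 = 0.585.
- Adjusted R² at that point = 1 − 0.415 × 23/15 = 0.363.
- An observed R² of exactly 0.50 gives F = (0.50/8)/(0.50/15) = 1.875, p = 0.14, and adjusted R² = 1 − 0.50 × 23/15 = 0.233.

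So the 0.50 threshold never binds. The rule reduces to the F test of R²=0.

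**3. How often the full rule is met, and what the fitted model then delivers.** The setting is N=24 with eight random normal predictors and least squares. The last column is from simulation with equal effects; mutual predictor correlation of 0 or 0.3 gives nearly the same values.

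| True R² | Mean apparent R² | Rule met | Median R² in new patients |
|---|---|---|---|
| 0 | 0.348 (= 8/23) | 5% | below 0 |
| 0.20 | 0.47 | 22% | below 0 |
| 0.30 | 0.53 | 37% | −0.08 |
| 0.40 | 0.60 | 56% | 0.07 |
| 0.50 | 0.66 | 75% | 0.23 |

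To reject a true R² of 0.50 or less at one-sided 0.025, the observed R² would have to be about 0.86.

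**4. With elastic net.** This simulation is illustrative (mixing 0.5, five-fold tuning, equal effects, independent predictors; 200 runs, 60 for nested cross-validation).
- No association: mean apparent R² is 0.12, and it reaches 0.50 in 6% of runs.
- True R² 0.30: apparent R² reaches 0.50 in 28%; nested cross-validated R² in none.
- True R² 0.50: apparent R² reaches 0.50 in 66%; nested cross-validated R² in about 10%. Median R² in new patients is about 0.20.

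**5. Using the validation cohort.** Least-squares coefficients are frozen and applied to 24 new patients, at true R² 0.50.
- One-df test of TIF on the frozen score, p<0.05: power 0.84.
- Predictive R² (1 − SSE/SST, no refitting) of at least 0.50: about 10%. At true R² 0.70 it is still only about 50%.

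**The case against.** The strongest reply is that the article never says the threshold applies to the apparent fit. It names elastic net and nested cross-validation, and nested resampling exists to estimate performance outside the fitting folds. If the 0.50 is meant for that R², the optimism objection largely falls away. This stands as a limit on the point: derivation-cohort use is an inference, from the order of the sentences and from a sample size that is the power of the ordinary F test. The alternative reading does not rescue the plan, however. The text ties cross-validation to deriving the model and not to the threshold, and neither the F-test p-value nor the 80% power carries over to a cross-validated R².

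Several stronger readings are tempting and are not supported:

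- **That the rule would pass pure noise.** A reader might infer this from the mean null R² of 0.35, or from the 14% chance that R² alone reaches 0.50. Both criteria must be met, and for the unpenalised fit that happens 5% of the time under no association. The 0.35, and the redundancy of the 0.50 cut-off, also belong to the unpenalised fit only. The weakness lies at true R² between 0 and 0.50.
- **That a failed validation would leave a declared success untouched.** No such declaration rule is stated. Both cohorts are sized from the same 50% criterion, and adjusted R² is to be reported with CIs, so a drop would be visible. What stands is that no validation criterion is given.
- **That the sample size is miscalculated.** It is not; 24 is correct for the test it powers.

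The article also acknowledges its limited sample size and presents the study as a platform for larger ones. That bears on how the result is interpreted; it does not settle which R² the rule governs.

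**Conclusion.** The point holds as a fault in where the decision rule sits and in what it can show. On the most natural reading, the sole success rule is judged in the 24 patients who build the model, and it amounts to a test of R²=0. Meeting it is evidence of some association. It is not evidence that the marker explains 50% of fibrosis, because it is met about 37% of the time at true R² 0.30 and 56% at 0.40. Even when the true R² is 0.50, the fitted least-squares model explains about 0.23 in new patients.

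These figures assume eight terms, normal random predictors and an unpenalised fit. The new-patient figure also assumes equal effects. Elastic net shrinks the optimism but leaves some of it, to an extent that depends on tuning choices the article does not fix.

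**What to change.** 1. Freeze the derivation coefficients. Base the primary conclusion on the validation cohort, using the one-df test of TIF on the frozen score (power about 0.84 at true R² 0.50, least-squares score).
2. Report predictive R² in that cohort (1 − SSE/SST, no refitting) with its 95% CI, set against the 0.50 target as an estimate.
3. Report derivation R² as descriptive only, beside its nested cross-validated or optimism-corrected value.
4. State in the Sample size calculation that the 80% power refers to rejecting R²=0, not to showing R² of at least 0.50.
5. Do not make predictive R² ≥ 0.50 a pass/fail gate without stating that, with 24 patients per cohort, it would be met only about 10% of the time at true R² 0.50.

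The cost is wording: both cohorts are already planned and no new data are needed. The downside is a less favourable headline figure. A formal demonstration of 50% explained variance in new patients would be a different matter, and cohorts of 24 cannot be expected to provide it.

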## Methods and analysis

### Study design

The NIMBLE-CKD study is an observational cohort study that aims to develop a novel non-invasive MRI biomarker to predict the percentage of kidney fibrosis quantified by histology in individuals with CKD. A control group will consist of healthy volunteers to establish normal kidney MRI parameters. This cohort will not undergo kidney biopsy due to unacceptable risk in a healthy population. An MRI model will be derived from a cohort of individuals with CKD who have undergone kidney biopsy, which will be validated against a second CKD participant cohort. CKD participants will be recruited consecutively and randomly assigned to either the derivation or validation cohorts, respectively. The study cohorts, timeline and procedures are outlined in figure 1.

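### Adjusted R² is the wrong statistic for validating a model with frozen coefficients, and with p undefined a raw validation R² of 0.50 could be reported as anything from 0.48 to 0.23

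*Protocol article*

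**What the plan says.** Under Study design, the Protocol article has a model derived in one biopsied CKD cohort, "which will be validated against a second CKD participant cohort". The Data analysis plan says the model is derived by elastic net with nested cross-validation. For the second cohort it names one statistic: "A second independent CKD participant validation cohort will be used to evaluate the accuracy and sensitivity of the model using adjusted R^2". It then adds: "The agreement performance of the model will be reported using adjusted R^2^ with 95% CIs".

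The only performance criterion is on plain R²: "Model performance will be assessed using a prespecified minimum variance (R^2^) threshold of 0.50 and p<0.05". It directly follows the sentence on developing the model in the derivation cohort. The sample size also rests on plain R²: "To detect a minimum of 50% variance (R^2^) explained by eight MRI variables", and "at a 0.05 level of significance and minimum power of 0.80, a sample of 24 subjects is required". The same number is carried to the second cohort: "Therefore, there will be 24 participants in each of the CKD participant derivation and validation cohorts".

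The article does not say which p enters the adjustment, or whether the coefficients are held fixed in the second cohort.

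**The concern.** The factor (n−1)/(n−p−1) in adjusted R² offsets the optimism that arises when p coefficients are fitted to the same n observations on which R² is computed. Predictions from a model fixed elsewhere carry no such optimism in the validation cohort, so the factor corrects for something that did not happen.

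Three further problems sit in the same two sentences:

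- After elastic net, p could be all eight variables, the terms retained, an effective number of degrees of freedom, or 1 if the composite marker is treated as a single predictor.
- Sensitivity is a property of a classification. No form of R² measures it for TIF scored from 0% to 100%.
- Agreement between predicted and observed TIF includes systematic over- or under-prediction. An R² from regressing TIF on the marker is blind to that.

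The validation cohort is half of the CKD sample and the study's only independent test of the model. The stated aim is to predict the percentage of fibrosis. As worded, the value reported for that test depends on a choice that the plan does not make.

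**Working it through.** **Inputs.** From Sample size calculation: n=24 per CKD cohort, eight MRI variables, R²=0.50, significance level 0.05, power 0.80. From Data analysis plan: adjusted R² as the validation and agreement statistic, and elastic net derivation.

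**The plan's own figure.** For the overall F test, f² = 0.50/(1 − 0.50) = 1.0, with noncentrality f²·N and degrees of freedom 8 and N−9. Power is 0.766 at N=23 and 0.801 at N=24, so the stated 24 reproduces. It is the size for an overall test of eight coefficients fitted in the same data, that is, for derivation.

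**The adjustment at n=24.** Adjusted R² = 1 − (1 − R²)·23/(23 − p). For a raw R² of 0.50:

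| p | Calculation | Reported |
|---|---|---|
| 1 | 1 − 0.50·23/22 | 0.477 |
| 3 | 1 − 0.50·23/20 | 0.425 |
| 5 | 1 − 0.50·23/18 | 0.361 |
| 8 | 1 − 0.50·23/15 | 0.233 |

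At p=8, a raw R² of 1 − 0.50·15/23 = 0.674 is needed to report 0.50, and any raw value below 1 − 15/23 = 0.348 is reported as negative. Without the penalty, 0.50 stays 0.50.

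**How far the readings diverge on the same data (illustrative).** This comes from 20,000 simulated derivation/validation pairs with 24 per cohort, eight independent and equally weighted predictors, population R² 0.50, and ordinary least squares in place of elastic net. Medians in the validation cohort:

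| What is evaluated | Raw R² | After adjustment |
|---|---|---|
| Correct coefficients, frozen (1 − SSE/SST) | 0.48 | 0.20 (p=8) |
| Coefficients estimated in derivation, frozen (1 − SSE/SST) | 0.18 | −0.25 (p=8) |
| Same frozen predictions, squared correlation | 0.35 | 1 − 0.647·23/22 = 0.32 (p=1) |
| Eight coefficients refitted in validation | 0.67 | 0.50 (p=8) |

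Row 2 gives the honest figure for the derived model, 0.18. Depending on the reading of adjusted R², the same study would report about −0.25, 0.32 or 0.50. The last value does not use the derived model at all. The gap between 0.18 and 0.35 is what re-estimating the intercept and slope conceals.

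**The case against.** The strongest defence is that the Outcomes section treats the multiparametric marker as one composite. Validation could then mean regressing TIF on that single frozen score, so that p=1 and 0.50 becomes 0.477, a trivial loss. This stands as a possible reading. A reader might infer that the plan forces a choice between a fall to 0.23 and a full refit, but the article fixes no p and the single-marker reading lies between the two. That reading still re-estimates intercept and slope in the validation data, so it recalibrates the model and cannot show agreement.

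A second defence is that plain R² can be recovered from adjusted R² once n and p are known. That holds only if p is reported, and only within the same form of R². A squared correlation cannot be turned back into 1 − SSE/SST.

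A third is that calibration and prediction error are commonly left to an analysis plan that is not shown. Their absence alone would be no finding. The article, however, does name the statistic for validation and for agreement, and it is unsuited to both. A fuller plan would have to contradict these sentences, not merely complete them.

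A reader might also infer that a good model would fail validation because its adjusted value falls below 0.50. The article states no 0.50 rule for the validation value: the threshold is on plain R² and sits with the derivation step. A false failure is a risk if the threshold is carried over informally. Nor does the article say that coefficients will be refitted. Finally, much of the shortfall in the simulation, from 0.48 to 0.18, comes from overfitting at n=24 and not from the choice of statistic.

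**Conclusion.** The concern holds. Adjusted R² is not a proper measure for a model whose coefficients come frozen from another cohort, and it measures neither sensitivity nor agreement. With n=24, a raw validation R² of 0.50 would be reported as anything from 0.48 (p=1) to 0.23 (p=8). If the eight coefficients are refitted, the adjustment is legitimate but nothing is validated.

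The range assumes that p does not exceed the eight variables of the sample size calculation, with the contrast distribution measures counted as one. The 0.23 is exact for n=24 and p=8 but is not a value the plan commits to. The simulated values rest on least squares and one scenario. Elastic net would change them, but it would not give the penalty a basis. The derivation-stage association test and the stated sample size are not affected by this point.

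**What to change.** In the Data analysis plan:

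1. State that all coefficients, and any centring and scaling of the MRI variables, are fixed from the derivation cohort before validation.
2. For the validation cohort, report unadjusted out-of-sample R² = 1 − SSE/SST on the frozen predictions, with a 95% CI from bootstrapping validation participants.
3. As the agreement measures, report RMSE in TIF percentage points and the calibration intercept and slope.
4. Delete *adjusted* and *sensitivity* from the validation sentence, and *adjusted* from the agreement sentence where it refers to validation.

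This costs a few lines of wording and trivial computation, with no new data and no change in sample size. Recruitment is expected to run to December 2028, so the change can be made before the validation data are analysed.

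### The primary R² and p value are not tied to one model: the plan describes both an all-variable linear regression and an elastic net

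*Protocol article*

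**What the plan says.** All of this comes from the Protocol article.

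- **Data analysis plan, the model:** "a multivariable linear regression model including all MRI variables will be fitted to examine the association between the multiparametric MRI marker and TIF".
- **Data analysis plan, where it is tested:** "The model will be tested and developed in the CKD participant derivation cohort".
- **Data analysis plan, the success rule:** "Model performance will be assessed using a prespecified minimum variance (R^2^) threshold of 0.50 and p<0.05".
- **Data analysis plan, later in the same paragraph:** "The multivariable linear regression model will be derived using elastic net regularisation and nested resampling cross-validation in order to minimise overfitting".
- **Outcomes:** "The model for the primary outcome will include the following MRI variables: total kidney volume, cortical T1 value, cortical T2 value, cortical T2* value". The list continues to eight items, with the cortical contrast measures counted as one.
- **Sample size calculation:** "To detect a minimum of 50% variance (R^2^) explained by eight MRI variables". With alpha 0.05 and power 0.80, the section arrives at 24 participants for each CKD cohort.

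The validation cohort is assessed by adjusted R², and agreement is to be reported as adjusted R² with a 95% CI. No p value is named for that cohort. The article does not say how a p value would be obtained from the elastic net.

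**The concern.** A full least-squares regression and an elastic net are different estimators. The first keeps every variable and has an overall F test with fixed degrees of freedom. The second shrinks coefficients, can set some to zero, and chooses its penalty from the data. It therefore has no fixed number of fitted parameters to put into an F test or an adjusted R².

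The success rule asks for an R² and a p value, and they could come from different fits. If the elastic net is the marker, the p<0.05 condition has no stated test behind it. If the full regression is tested, the p value is sound but belongs to a model that is not the marker. At stake is whether the primary outcome is declared met, because the choice of fit could be made after the results are known.

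**Working it through.** **1. Which model the sample size belongs to.** The inputs from the Sample size calculation are R² = 0.50, eight predictors, alpha 0.05 and power 0.80.

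- Effect size: f² = 0.50/(1 − 0.50) = 1.
- Degrees of freedom at n = 24: 8 and 24 − 9 = 15.
- Noncentrality: f² × n = 24.
- Power of the overall F test: 0.766 at n = 23 and 0.801 at n = 24.

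The smallest sufficient n is 24, so the plan's figure is reproduced. It is the figure for the unpenalised model with all eight variables.

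**2. What the rule means in that model.** The p<0.05 boundary in terms of R² is 8F/(8F + 15), with F the 5% critical value on 8 and 15 df. This gives R² = 0.585. An observed R² of exactly 0.50 gives:

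- F = (0.50/8)/(0.50/15) = 1.875, with p = 0.14;
- adjusted R² = 1 − 0.50 × 23/15 = 0.233.

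In the full regression the 0.50 threshold therefore never binds. The joint rule reduces to the F test, which holds its 5% level.

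**3. What the rule means after elastic-net selection.** The article gives no tuning settings, so the following are assumptions: n = 24, eight equicorrelated normal predictors unrelated to TIF, mixing 0.5, five-fold tuning at minimum error, then a least-squares refit of the retained variables with an ordinary F test in the same data. The plan does not state the refit. There were 1,500 runs per row.

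| Predictor correlation | p<0.05 alone | p<0.05 and R² ≥ 0.50 |
|---|---|---|
| 0 | 25.8% | 7.5% |
| 0.3 | 21.7% | 6.5% |
| 0.6 | 20.3% | 6.7% |

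Across these and shorter runs with other tuning folds, the ranges are about 20-32% for p alone and about 6-9% for the joint rule. If R² is taken from the shrunken elastic-net predictor instead of the refit, the joint rule is met in about 3-5%. In 200 null runs, no nested cross-validated R² reached 0.50.

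**4. Whether the readings agree when there is a real effect.** The assumptions are n = 24, eight equal-effect predictors, true R² = 0.50, five-fold tuning inside six-fold outer cross-validation, and 200 runs per setting (standard error about 3 points).

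| Reading of the rule | Correlation 0.3 | Correlation 0 |
|---|---|---|
| Full regression, R² ≥ 0.50 and p<0.05 | 69% pass | 76% pass |
| Nested cross-validated R² ≥ 0.50 | 12% pass | 7% pass |
| Datasets where these two disagree | 57% | 69% |

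With correlation 0.3, the refit of retained variables passed the joint rule in 82%. The full-regression rates are in line with the 0.749 power obtained when predictors are treated as random.

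**The case against.** The strongest defence is that there is only one model. An elastic net is a penalised linear regression. The sentence on derivation can refer back to the model already introduced, and the references to all variables can mean the candidate inputs. A sample size taken from the eight-variable F test would then be a planning approximation. This reading is possible and softens the wording conflict. It does not remove the problem, because p<0.05 is then attached to a tuned, penalised fit in its own development data with no test named.

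A second defence is that tuning and inference details belong in an analysis plan that is not shown. That is fair for fold counts and mixing values, and their absence is no criticism here. But the article itself states the estimator, threshold, p criterion and cohort, and those statements are what need reconciling.

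A third defence is that the harm is limited, and this largely stands. A reader might infer from the 20-32% figure that the trial has a one-in-four chance of a false primary claim. The document does not support that: the rate is for p<0.05 alone, it assumes an unstated refit, and the plan also requires R² of at least 0.50. A randomly assigned validation cohort of 24 gives further protection, although no p criterion is attached to it.

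**Conclusion.** The point holds as a should-fix. The primary R² and p value are not tied to one fit, and the sized model is not clearly the model that defines the marker. Under the assumed settings, the false-positive rate of the plan's own joint rule is about 6-9% with a refit and about 3-5% with the elastic-net R², against 5% for the full regression. That inflation is modest. The larger consequence is that admissible readings disagreed in 57-69% of simulated datasets with a true R² of 0.50.

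Two further inferences should be avoided. The sample-size arithmetic is not wrong; it reproduces, but for the unpenalised model. Nor is a p value impossible for an elastic net: valid ones exist, and the article names none. The percentages depend on the assumed mixing, folds, correlation and refit. The conflict in the text does not.

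**What to change.** Name one primary estimator, and state which fit and which cohort supply R² and p. If it is the elastic net:

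- Define the multiparametric marker as the elastic-net linear predictor.
- Either take R² from the nested cross-validation and p from a permutation test that permutes TIF and reruns the whole tuning pipeline, or freeze the score and use its one-df test in the validation cohort (1 and 24 − 2 = 22 df), with its R² and CI.
- Report the unpenalised all-variable regression as a sensitivity analysis, and do not use its F test or in-sample adjusted R² as the primary criterion.

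If the full regression is to be primary, say so, define the marker as its fitted value, and make the elastic net secondary.

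The cost is wording and computing time. The elastic-net route will also show a less favourable R² than the in-sample value: in the simulations above, a nested R² of 0.50 was reached in only 7-12% of datasets even with a true R² of 0.50. The chance of meeting the 0.50 threshold should therefore be restated for whichever R² is chosen. Study status expects recruitment to run to December 2028, so this can be settled before analysis.
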